## Abstract

**Background:**

Early palliative/pre-emptive intervention improves clinical outcomes and quality of life for patients with metastatic cancer. A previous signal-seeking randomized controlled trial (RCT) demonstrated that early upfront radiotherapy to asymptomatic or minimally symptomatic high-risk osseous metastases led to reduction in skeletal-related events (SREs), a benefit driven primarily by subgroup of high-risk spine metastasis. The current RCT aims to determine whether early palliative/pre-emptive radiotherapy in patients with high-risk, asymptomatic or minimally symptomatic spine metastases will lead to fewer SREs within 1 year.

**Methods:**

This is a single-center, parallel-arm, in-progress RCT in adults (≥ 18 years) with ECOG performance status 0–2 and asymptomatic or minimally symptomatic (not requiring opioids) high-risk spine metastases from histologically confirmed solid tumor malignancies with > 5 sites of metastatic disease on cross-sectional imaging. High-risk spine metastases are defined by the following: (a) bulkiest disease sites ≥ 2 cm; (b) junctional disease (occiput to C2, C7-T1, T12-L2, L5-S1); (c) posterior element involvement; or (d) vertebral body compression deformity > 50%. Patients are randomized 1:1 to receive either standard-of-care systemic therapy (arm 1) or upfront, early radiotherapy to ≤ 5 high-risk spine lesions plus standard-of-care systemic therapy (arm 2), in the form of 20–30 Gy of radiation in 2–10 fractions. The primary endpoint is SRE, a composite outcome including spinal fracture, spinal cord compression, need for palliative radiotherapy, interventional procedures, or spinal surgery. Secondary endpoints include (1) surrogates of health care cost, including the number and duration of SRE-related hospitalizations; (2) overall survival; (3) pain-free survival; and (4) quality of life. Study instruments will be captured pre-treatment, at baseline, during treatment, and at 1, 3, 6, 12, and 24 months post-treatment. The trial aims to accrue 74 patients over 2 years to achieve > 80% power in detecting difference using two-sample proportion test with alpha < 0.05.

**Discussion:**

The results of this RCT will demonstrate the value, if any, of early radiotherapy for high-risk spine metastases. The trial has received IRB approval, funding, and prospective registration (NCT05534321) and has been open to accrual since August 19, 2022. If positive, the trial will expand the scope and utility of spine radiotherapy.

**Trial registration:**

ClinicalTrials.Gov NCT05534321. Registered September 9, 2022.

**Trial status:**

Version 2.0 of the protocol (2021-KOT-002), revised last on September 2, 2022, was approved by the WCG institutional review board (Study Number 1337188, IRB tracking number 20223735). The trial was first posted on ClinicalTrials.Gov on September 9, 2022 (NCT05534321). Patient enrollment commenced on August 19, 2022, and is expected to be completed in 2 years, likely by August 2024.

**Supplementary Information:**

The online version contains supplementary material available at 10.1186/s13063-023-07850-8.

## Background

Spine metastases are a common occurrence in many solid tumors, with bone being the third most common organ affected by metastatic disease [1]. Spine metastases are a prominent source of cancer-related morbidity and mortality, despite standard of care treatment [2], and the associated pain commonly impairs function and decreases quality of life. High-risk spine metastases, despite initially being asymptomatic or minimally symptomatic, can also result in more debilitating complications, such as pathologic fractures and spinal cord compression [3]. These skeletal-related events (SREs) are frequently addressed with palliative radiation therapy (RT) [4–6]. However, once a patient’s spinal metastases become severely symptomatic or result in SREs, it is significantly more difficult to return the patient to a low baseline pain burden [7]. The current standard of care in patients with minimally symptomatic (non-opioid medication dependent) spine metastases is to continue systemic therapy or observation with medical management for pain and referral for consideration of palliative RT only when the metastases become significantly symptomatic or result in SRE. This regimen in patients with high-risk spine metastasis warrants re-evaluation because adequate symptom reversal is not achieved in the majority of patients treated with the traditional paradigm.

SREs are defined as pathological spinal fractures, spinal cord compression, and the need for interventions, such as RT, interventional procedures, or surgical interventions. SREs significantly impact health-related quality of life in patients with metastatic disease. These events are a measurable primary outcome and have been used as standard primary endpoints in clinical trials investigating therapies for bone metastases [8, 9]. In a recent study, the baseline rate of SREs in patients with metastatic solid tumors with bone metastases was approximately 65% at 1 year, with the median time to SREs being 155 days [10]. SREs also present a socioeconomic burden and lead to significant healthcare utilization and cost [11–13].

Early palliative treatment has been demonstrated to improve the quality of life and even survival for patients with metastatic cancer [6]. Many specialized centers now advocate for earlier integration of RT in a patient’s treatment course, especially with patients living longer with their systemic disease. While several RCTs have evaluated the efficacy and safety of varying RT regimens for managing symptomatic bone lesions, few studies so far have examined the utility of early, upfront RT for the treatment of asymptomatic or minimally symptomatic spine metastases. It is however known that RT can significantly reduce the risk of SREs in patients with solid tumors metastasizing to the bone [14]. A phase 2, multicenter randomized controlled trial recently evaluated the role of early prophylactic RT in patients with high-risk bone metastases, including spine metastases, in patients with polymetastatic disease [14]. In this study, 78 patients with 122 high-risk bone metastases were enrolled and randomized to systemic therapy or observation, in addition to early prophylactic RT. At 1 year, SREs occurred in 1 of 62 lesions (1.6%) in the RT arm and 14 of 49 lesions (29%) in the standard-of-care systemic therapy arm (*P* < 0.001). Specific high-risk features were associated with a significant difference in the time-to-SRE, with most SREs seen in junctional or bulky (> 2 cm) spine disease (*P* = 0.016). Given this intriguing signal, the primary aim of the current randomized trial is to determine whether upfront, early palliative or pre-emptive RT, compared to standard-of-care systemic therapy in patients with high-risk asymptomatic or minimally symptomatic (non-opioid dependent) spine metastases leads to fewer SREs.

## Methods

### Study design and setting

This is a single-center, parallel-arm, prospective, superiority design, randomized controlled trial in patients with asymptomatic or minimally symptomatic high-risk spine metastasis from solid tumors. The study protocol has been reported following the “Standard Protocol Items: Recommendations for Clinical Interventional Trials” (SPIRIT) guidelines along with SPIRIT-Outcomes reporting recommendations (see Supplementary file 1) [15, 16]. This single-center study will be carried out at Miami Cancer and Neuroscience Institutes, Baptist Health South Florida, which represent a hybrid community-academic hospital in Miami, FL, USA (RRID:SCR_023294). Miami Cancer Institute represents one of the largest free-standing cancer hospitals in the state of Florida and has a diverse patient including, particularly of Hispanic or Latino ethnicity [17]. Subjects in this study are randomized to receive either standard-of-care systemic therapy or upfront, early RT to high-risk spine lesions followed by standard-of-care systemic therapy.

### Inclusion criteria

Eligibility criteria for participants in this trial have been informed by prior trials of spine radiotherapy. Included participants must fulfill each of the following inclusion criteria:Histologically confirmed polymetastatic solid tumor, i.e., with > 5 sites of metastatic disease as seen on cross-sectional imagingAsymptomatic or minimally symptomatic (not requiring opioids) spinal metastases that have high risk features as per the Spinal Instability Neoplastic Score (SINS) framework. These include (i) bulky osseus disease sites, i.e., ≥ 2 cm; (ii) junctional spine disease, including the thoracic apex (Occiput to C2, C7-T1, T12-L2, and L5-S1); (iii) posterior element involvement, including interspinous, unilateral, or bilateral facet joints; (iv) compression deformity of > 50% of the vertebral body [3]Performance status of 0–2 as per the Eastern Cooperative Oncology Group (ECOG) scaleAge ≥ 18 yearsCapacity to provide informed consent for trial participationParticipants of reproductive potential must agree to utilize an effective contraceptive method. Individuals of childbearing potential must not be lactating or pregnant

### Exclusion criteria

All participants with polymetastatic disease with high-risk spine metastases from solid tumor malignancies are eligible for enrolment in this study, except for the following exclusion criteria:Participant having received RT previously to the intended lesion which precludes the use of RT plan in the current study based on standard tissue tolerance to RTSignificant medical comorbidities that preclude the use of RTParticipants that are pregnant or lactatingTarget lesion(s) for spine RT is/are complicated metastases with clinical or radiological features of cord compression or impending pathological fractureParticipants having leptomeningeal disease, i.e., tumor metastasis to the arachnoid and pia materParticipants whose entry to the trial will cause unacceptable clinical delays in their planned management

### Study endpoints

The endpoints selected in this trial have been utilized by similar trials [10, 14] and are defined within the time window from the date of randomization to death or 12 months, whichever occurs first. The primary endpoint of the study is the number of SREs per arm, which is defined as pathological fractures, spinal cord compression, or interventions (palliative RT, interventional procedures, or spine surgery) at 12 months. The secondary endpoints are as follows:Surrogates of health care cost, including the number and the duration of hospitalizations for SREsPain, as assessed using Brief Pain Inventory (BPI) short-form questionnaireHealth-related quality of life, as assessed using the Functional Assessment of Cancer Therapy-General (FACT-G) and the 5-level EuroQoL-5D (EQ-5D-5L)Median pain-free survival (PFS), defined as the time from study entry to the start of opioids or death. This definition has been utilized on basis of Rosen et al. [10]Median overall survival (OS), defined as the time from study entry to death or censoring due to follow-up

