### Power calculation

Power calculation has been performed by a formally trained institutional biostatistician, based on the primary endpoint of the rate of SREs from the date of participant randomization to their death or 12 months follow-up, whichever occurs first, in the two trial arms. SRE, a composite outcome measure, has been defined as a pathological spine fracture, spinal cord compression, or warranting of a procedure (palliative RT, interventional procedures, or spine surgery). SRE is a binary variable, where the event rate may be defined as the number of spine lesions with SRE occurrence divided by the total number of target spine lesions identified. Given the lesion-based analysis in the current trial, occurrence or non-occurrence of an SRE at one vertebra does not impact the status of other spine lesions within the same individual.

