Based on institutional records and previous trials, it is estimated that nearly 60–80% of patients may be successfully followed up for at least 1 year. For the standard of care trial arm, where only routine medical management is done, the rate of SRE is known to be nearly 60% within 1 year. Meanwhile, it is known that approximately three fourths of inpatient radiation consultations for painful bone metastases have been reported to lead to palliative RT. Furthermore, prior studies indicate that nearly 60% of RT-targeted spine lesions had been diagnosed ≥ 4 months prior to RT [7]. Therefore, we believe a 60% estimated event rate (as defined above) at 1 year is a conservative estimate. For the investigational trial arm, where early prophylactic RT is being provided to high-risk spine metastases, an SRE rate of 30% is estimated. The efficacy of RT in controlling pain from spine metastases is well-known. Since RT targets and mitigates, to a certain extent, the pathologic effect of a spinal metastases, this leads to reduced development of major bony pain, which is often a causative factor for SREs. For these SRE rates, inclusion of at least 66 individuals with evaluable SRE endpoints in a 1:1 randomization will allow the trial to achieve > 80% power based on a one-sided, two-sample proportion test with significance level of 0.05. Given that the individuals who withdraw prior to the SRE endpoint occurring may not evaluated as per the trial plan; therefore, a per-protocol analysis will be carried out. The limitations of the per-protocol analysis are mitigated by the use of hard endpoints in the current study along with the high morbidity and dismal prognosis of the participants. In order to ensure a minimum of 33 participants are enrolled per trial arm, we plan to over-accrue by 10%, so that the trial is sufficiently powered for the primary endpoint, resulting in a planned sample size of *N* = 74 participants. Additionally, we note that the unit of analysis is the spine lesion, and a small subset of patients may have multiple evaluable lesions (SREs). Since each lesion will be included separately in the analysis, therefore, the final sample size for the primary endpoint may be higher than estimated. We expect to enroll all 74 participants within 2 years.

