### Discontinuation of study intervention

Early discontinuation is considered for a patient based on the patient’s and treating physician’s decision for standard of care therapies. Protocol treatment is discontinued when there is systemic or local progression of disease resulting in hospice enrollment.

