### Planned statistical analysis

The primary objective of this study is to compare the rate of SREs from the date of randomization to mortality or 1 year, whichever occurs first, between participants receiving standard of care therapies versus participants receiving palliative RT for high-risk spine metastases. It is expected that nearly 60% of the enrolled participants will have at least 1 year of follow-up. The primary endpoint, SRE, has been previously defined as a composite measure including pathological spine fractures, spinal cord compression, or need of spinal interventions (palliative RT, or orthopedic surgery). SRE is a binary variable, with the rate of SRE defined as the number of lesions having SRE divided by the total number of eligible spine lesions. Given that this analysis is lesion-based, not participant-based, therefore, occurrence or non-occurrence at one lesion does not impact the status of other lesions in the same participant. Around 15% of participants may have multiple lesions, for which each lesion gets evaluated as an independent unit of analysis. Meanwhile, unlike the primary objective, the secondary objectives will be evaluated per participant.

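### The primary SRE proportion counts an SRE-free death as a full success, leaves evaluability undefined, and names no analysis that separates SRE prevention from survival

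*Protocol article*

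**What the plan says.** Study endpoints says the endpoints are "defined within the time window from the date of randomization to death or 12 months, whichever occurs first". Power calculation and Planned statistical analysis repeat that window for the primary endpoint and treat SRE as binary. The rate is "the number of spine lesions with SRE occurrence divided by the total number of target spine lesions identified" in the first of these sections and "the number of lesions having SRE divided by the total number of eligible spine lesions" in the second.

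Power calculation assumes that in the control arm "the rate of SRE is known to be nearly 60% within 1 year" and that with RT "an SRE rate of 30% is estimated". It sizes the trial on "at least 66 individuals with evaluable SRE endpoints", without saying what makes an endpoint evaluable. It adds that patients who withdraw before an SRE may not be evaluated, and it plans a per-protocol analysis. It expects 60–80% of patients to be followed for a year. Planned statistical analysis gives the lower end: "It is expected that nearly 60% of the enrolled participants will have at least 1 year of follow-up". Over-accrual is 10%, from 66 to 74.

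Log-rank tests are planned for pain-free and overall survival. No time-to-SRE analysis is named.

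**The concern.** Read literally, the counting rule keeps an SRE-free death in the denominator as a non-event. That is a legitimate quantity, the risk of an SRE in the presence of death, but it depends on survival as well as on SRE prevention. If one arm loses more patients early, its lesions have less time to produce an SRE and its rate falls without any SRE having been prevented. If RT patients live longer, they have more time at risk and a real effect is diluted.

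The power section adds an uncertainty. Because evaluable is undefined, an analyst could keep SRE-free deaths or drop them. Dropping patients who withdraw before an SRE also discards their SRE-free time while keeping those who had an event first, which pushes the observed rate up. The article settles the role of death for pain-free survival, where death is an event, but does not say expressly how a death without an SRE enters the primary rate.

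**Working it through.** **The plan's own figure.** For 60% vs 30%, one-sided 0.05 and 80% power, with a pooled-variance two-proportion test:

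n per arm = [1.645·√(2·0.45·0.55) + 0.842·√(0.6·0.4 + 0.3·0.7)]² / 0.30² = 32.9, so 33 per arm and 66 in total. Power at 33 per arm is 80.1%. Then 66/0.9 = 73.3, rounded up to 74. The stated size reproduces.

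**Does evaluable mean followed for a year?** If it did, 74 enrolled would yield 74 × 0.60 = 44 to 74 × 0.80 = 59 evaluable patients, and 66 evaluable would need 66/0.80 = 83 to 66/0.60 = 110 enrolled. The 10% over-accrual therefore fits only if most patients without a full year, deaths included, are evaluable.

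**Scenario for the two counting rules.** These are assumptions, because the documents give no death rate:
- constant, independent hazards, and one lesion per patient;
- 60% and 30% are 12-month SRE risks in the absence of death;
- 12-month mortality d = 20–40%, so everyone without a year of follow-up has died. This is an upper bound, with d = 10% shown beside it.

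SRE hazards per year: λ = −ln(0.4) = 0.916 (control) and −ln(0.7) = 0.357 (RT). Death hazard: μ = −ln(1 − d), which is 0.105, 0.223 and 0.511 at 10%, 20% and 40%.

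- Deaths kept as non-events: F = λ/(λ+μ) · (1 − e^−(λ+μ))
- Death before any SRE: D = μ/(λ+μ) · (1 − e^−(λ+μ))
- SRE-free deaths dropped: F/(1 − D)

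| Deaths by 12 months | Control kept / dropped | Gap | RT kept / dropped | Gap |
|---|---|---|---|---|
| 10% | 57.4% / 61.5% | 4.1 | 28.6% / 31.2% | 2.6 |
| 20% | 54.7% / 63.1% | 8.4 | 27.1% / 32.6% | 5.5 |
| 40% | 48.8% / 67.0% | 18.2 | 23.8% / 36.2% | 12.4 |

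These gaps are between two counting rules within one arm. They are not changes in the treatment effect, and they differ by arm even when mortality is equal, because they depend on the SRE rate.

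**Arm difference, equal mortality.** Kept: 27.6 points at 20% deaths and 24.9 at 40%. Dropped: 30.5 and 30.8. The choice of rule changes the contrast by about 3 to 6 points.

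**Arm difference, unequal mortality.** With no RT effect (60% risk without death in both arms) and deaths of 20% control / 40% RT, the kept rule gives 54.7% vs 48.8%, a false 5.9-point benefit for RT. The dropped rule gives 63.1% vs 67.0%, 3.9 points the other way. With the planned effect and deaths of 40% control / 20% RT, the contrast is 21.7 points (kept) or 34.4 (dropped).

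**Power, deaths kept, equal mortality.** With 37 per arm (all 74), 79% at 20% deaths and 73% at 40%. With 33 per arm, 75% and 68%.

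**The case against.** The strongest reply is that the counting rule is already there: the window closes at death and the denominator is all target lesions, so an SRE-free death is a non-event. That is the natural reading, and the 10% over-accrual supports it. A reader might infer that the power section contradicts it by tying evaluability to a year of follow-up. The text does not support that. The follow-up sentence stands apart, and the only patients named as possibly not evaluated are those who withdraw. What remains is an undefined term and a rule that drops withdrawals.

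A reader might also infer that hospice entry makes a patient SRE-free or unevaluable. The discontinuation section says only that "Protocol treatment is discontinued when there is systemic or local progression of disease resulting in hospice enrollment". It ends treatment and does not close the endpoint window, so hospice is no part of this point.

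The size is open to challenge as well. The 8–18 points need every shortfall in follow-up to be a death. The false benefit needs mortality to double in the RT arm, whereas the article expects no significant excess of deaths there. At 20% vs 25% mortality the same calculation gives a false difference of 1.4 points. If the assumed 60% and 30% are observed rates that already include deaths, the power loss disappears. All of this stands and limits the claim.

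Finally, overall survival is compared, so an imbalance in deaths would be seen, and supportive analyses could sit in a fuller plan. But seeing an imbalance does not show how much of an SRE difference it explains, and the article itself fixes the crude proportion and the dropping of withdrawals.

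**Conclusion.** The concern holds in a limited form. The primary rate mixes SRE risk with survival, the term evaluable is undefined, and patients who withdraw before an SRE may be dropped in a trial that expects 20–40% not to complete a year. This is an ambiguity and an improvable method, not a contradiction.

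The size is a scenario range. The within-arm gap between counting rules is 8–18 points (control) and 5.5–12 (RT) at 20–40% deaths, or 2.6–4.1 points at 10%. The arm contrast changes by about 3–6 points under equal mortality. A false benefit near 6 points arises only under a marked mortality imbalance. It would be wrong to say that the trial's SRE rate will move by up to 18 points, since no death rate is given and the treatment contrast moves far less when mortality is equal. The point is worth acting on because the change is cheap and is best fixed before outcomes are known.

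**What to change.** 1. In Power calculation and Planned statistical analysis, define evaluable and state that a target lesion in a patient who dies without an SRE stays in the denominator as a non-event, with death as a competing event.
2. Estimate the 12-month SRE rate per arm by Aalen-Johansen cumulative incidence. Censor living patients at last contact instead of dropping those who withdraw before an SRE, and cluster the variance by patient.
3. Report beside it the cause-specific hazard ratio for time to SRE and SRE-free survival (SRE or death) by arm. These are needed because, with complete follow-up, the cumulative incidence equals the crude proportion with deaths as non-events. It repairs the handling of withdrawals but does not by itself show whether a difference comes from deaths.
4. State the assumed 12-month mortality and whether 60% and 30% already include deaths. If they do not, restate power (about 73–79% with 37 per arm at 20–40% equal mortality). Explain how 60–80% one-year follow-up fits with 10% over-accrual.

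The cost is wording, one changed estimator and two supportive analyses. Death dates are already needed for overall survival, and SREs are recorded when they occur. The downside is a little more analysis and possibly a slightly lower stated power.

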### Rationale for study instruments and endpoints

This trial is investigating the impact of early, upfront RT on the number of SREs occurring in participants with high-risk spine metastases. The clinical rationale for using SREs as the primary endpoint has been addressed previously and is further expanded here. It has been demonstrated that once a patient’s spinal metastases become severely symptomatic, it is significantly more difficult to return the patient to a low pain burden with treatment compared to when the lesions were less symptomatic [7]. Additionally, in a recent multicenter study that aimed to describe differences in health resource utilization of SREs across Europe and the USA, nearly 25% of reported SREs were found to warrant inpatient hospitalization with a mean length of stay of 18 days [12]. In this work, over 95% of SREs led to procedural management, of which bone RT was the most frequent. Similarly, another investigation demonstrated that nearly a quarter of all SREs warranted an inpatient admission with a mean length of stay of 19.5 days [13]. Furthermore, it has also been demonstrated that efforts to prevent SREs from occurring considerably lead to cost-reduction related to managing SREs, given the substantial economic cost of interventions warranted [11]. Finally, these events also lead to significant utilization of health resources and a major socioeconomic burden [12, 13]. Therefore, on basis of their clinical, economic, and patient-centric utility, SREs have been chosen as the primary endpoint.

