### Study interventions

All participants in the current study receive systemic therapy as per the standard of care, while arm 2 also receives RT. The specifics of RT, target volume, and organ-at-risk delineation and plan evaluation is performed according to institutional standards. For this protocol, total dose and dose fractionation may be delivered at the discretion of the treating radiation oncologist. All techniques, including conventional, 3D conformal RT (3D-CRT), intensity-modulated RT (IMRT), or SRS techniques may be used, with or without image guidance, as deemed appropriate.

Participants undergo RT to each lesion using one of the dose and fractionation regimens presented in Table 1. A variety of dose fractionation schedules including conventional palliative doses as well as SRS schedules are allowed per protocol. After using appropriate immobilization, a simulation is captured for all participants followed by conduct of a CT or MR imaging in the treatment position. The radiation oncologist determines the utilization, if any, of oral or intravenous contrast.

**Table 1 Tab1:** Dose and fractionation of radiotherapy in the PROMISSED trial

Total dose	Fractions	Dose per fraction	Verification
2000 cGy	5	400 cGy	MV or KV or MR
3000 cGy	10	300 cGy	MV or KV or MR
3000 cGy	5	600 cGy	KV and CBCT or MR
2400 cGy	3	800 cGy	KV and CBCT or MR
2700 cGy	3	900 cGy	KV and CBCT or MR
2400 cGy	2	1200 cGy	KV and CBCT or MR

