A Wilcoxon rank-sum test will be utilized to compare the number of hospitalizations secondary to SREs between the trial arms. For comparing the quality of life and pain level between the trial arms, we will assess at 3 months, 6 months, 12 months, and within 1 week of any SRE (optional). The individual and overall scores derived from the scales described previously will be summarized at these assessment points using means and standard deviations, or medians, and inter-quartile ranges. We will evaluate categorical variables from EQ-5D-5L between the trial arms using Fisher’s test at each time point as well, from which we will determine odds ratios with 95% confidence intervals. We will summarize other non-quantifiable answers (such as treatment received for pain control) in a descriptive fashion. For the score for pain interference on the BPI Short Form scale, we will consider it as the average of the seven interference questions as long as ≥ 4 questions are complete. The mean difference between the trial arms with regard to scores on these scales will be assessed for both statistical and clinical significance. This will be done using Wilcoxon rank-sum tests and established MCIDs. For scales lacking established MCIDs, the “half standard deviation” rule will be applied, wherein the differences of a half standard deviation in the scores between trial arms considered clinically meaningful. After the study is completed, we will plot data at each assessment point, including the number of trial participants in each arm, mean scale scores, and their trends over time. Based on this, we will consider utilizing more exhaustive regression analyses including generalized linear models. We will utilize log-rank tests to compare time-to-event endpoints such as PFS and OS. For toxicity, we will tabulate all AEs at 3, 6, 12, and 24 months post-randomizations in the early upfront RT arm.

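### The named cost surrogates are hospitalizations for SREs only; they omit the up-front RT given in arm 2 and most SRE care, so they cannot alone support a net cost conclusion

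*Protocol article*

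**What the plan says.** The Study endpoints section gives, as the first secondary endpoint, "Surrogates of health care cost, including the number and the duration of hospitalizations", and limits these to hospitalizations for SREs. The abstract says the same: "surrogates of health care cost, including the number and duration of SRE-related hospitalizations". In Planned statistical analysis the one comparison tied to this endpoint is: "A Wilcoxon rank-sum test will be utilized to compare the number of hospitalizations secondary to SREs between the trial arms". The article names no other resource item as a cost surrogate and describes no other cost analysis.

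The arms differ by the intervention itself. Study interventions states: "All participants in the current study receive systemic therapy as per the standard of care, while arm 2 also receives RT". The abstract describes that treatment as given to up to five lesions, "in the form of 20–30 Gy of radiation in 2–10 fractions".

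The section on the rationale for instruments and endpoints cites two studies of resource use. In the first, "nearly 25% of reported SREs were found to warrant inpatient hospitalization with a mean length of stay of 18 days", and "over 95% of SREs led to procedural management, of which bone RT was the most frequent". In the second, "nearly a quarter of all SREs warranted an inpatient admission with a mean length of stay of 19.5 days".

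**The concern.** An endpoint labeled as a surrogate of health care cost should be able to move in either direction when the new strategy consumes resources of its own. The named measure can register a saving from early RT, through fewer SRE admissions, but not what early RT uses. Three kinds of resource fall outside it:

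- the up-front RT, which by design goes to arm 2 only;
- RT and procedures for SREs managed without admission, which by the article's own figures is most SRE care;
- admissions for causes other than an SRE, including any from RT toxicity.

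What remains is close to a count of a subset of primary-endpoint events. If it falls in arm 2 and is reported under the heading of cost, readers may take it as evidence that early RT lowers health care cost overall. The measure cannot show that.

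**Working it through.** **The plan's own figure.** The article gives no figure for the cost endpoint. Its primary sample size does reproduce: 60% vs 30%, one-sided 0.05, pooled variance without continuity correction, gives 33 per arm (66) with 80.1% power, and 66 / (1 − 0.10) = 73.3, rounded up to 74, or 37 per arm. It is used below only for the number of patients.

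**Inputs.** 37 per arm and SRE rates of 60% and 30% at 1 year (Power calculation); about 25% of SREs admitted, mean stay 18 or 19.5 days, over 95% managed by a procedure (rationale section); 2 to 10 fractions per course (abstract).

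**Assumptions, not in the plan.** One lesion and at most one SRE per patient; the same admission share and stay per SRE in both arms; every arm 2 patient receives up-front RT.

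**Share of SRE care missed.** About 1 − 0.25 = 75% of SREs produce no counted event. The 25% and 95% figures come from the same cited study, so at least about 0.95 − 0.25 = 70% of its SREs had a procedure and no admission.

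**What the measure counts.**

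| | Arm 1 | Arm 2 |
|---|---|---|
| SREs | 37 × 0.60 = 22.2 | 37 × 0.30 = 11.1 |
| SRE admissions, 25% admitted | 5.6 | 2.8 |
| Range, 20% to 30% admitted (assumed) | 4.4 to 6.7 | 2.2 to 3.3 |
| Days, 25% admitted, 18-day stay | 99.9 | 50.0 |
| Days, 25% admitted, 19.5-day stay | 108.2 | 54.1 |
| SREs not admitted (uncounted) | 16.7 | 8.3 |

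The counted admissions halve because the SREs halve.

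**What it does not count.** Arm 2 has 37 up-front RT courses at one per patient, which is 37 × 2 = 74 to 37 × 10 = 370 fractions. In the comparison kindest to arm 2, every arm 1 SRE is irradiated and no arm 2 SRE is: 22.2 vs 37 courses, still 14.8 more in arm 2. If the same share of SREs receives RT in both arms (assumed):

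| Share of SREs given RT | Arm 1 courses | Arm 2 courses |
|---|---|---|
| 50% | 11.1 | 37 + 5.6 = 42.6 |
| 75% | 16.7 | 37 + 8.3 = 45.3 |
| 95% | 21.1 | 37 + 10.5 = 47.5 |

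RT use therefore points the opposite way to the counted endpoint throughout.

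**How firm the tilt is.** With 0.60 × 0.25 = 15% vs 0.30 × 0.25 = 7.5% of patients having an SRE admission and 37 per arm, simulation gives fewer admissions in arm 2 in about 80% of trials, a tie in 9% and more in 11%. If arm 2 SREs were admitted at 50% instead of 25% (assumed), 0.30 × 0.50 = 15% equals the arm 1 figure and the expected difference is zero although SREs halve. Power to detect 15% vs 7.5% with any SRE admission, two-sided 0.05, is about 16% with 33 per arm and 17% with 37.

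**The case against.** A reader might infer that the plan deliberately excludes all other resources and that the result must favor RT whenever SREs fall. The documents do not support either reading. Both statements of the endpoint introduce the hospitalization items with *including*, so the list is formally open, and a fuller protocol or analysis plan may add items. The measure follows SRE admissions rather than SREs: it favors RT in expectation only if admission share and stay per SRE are similar between arms, and with roughly 3 to 6 admissions per arm chance can reverse it. At 16–17% power, a statistically significant finding of fewer SRE admissions is also unlikely on these figures.

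It can also be said that the article poses no net-cost or cost-effectiveness question. The aim is fewer SREs, the item is one secondary endpoint called a surrogate, and the Discussion makes no cost claim. The cost argument in the rationale concerns the cost of managing SREs, for which SRE admissions are a direct if partial marker. Palliative RT, interventional procedures and spine surgery are recorded as primary-endpoint components, up-front RT is known from the assigned treatment, and arm 2 toxicity is tabulated. Much of the missing information is thus in the trial, though not in the named cost measure.

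A reader might further infer biased attribution of admissions to SREs. The article says that the treating physician and the participant know the arm; it does not say who attributes an admission, so that remains an inference. Finally, the counts above apply lesion-level rates to patients, and around 15% of participants are expected to have several lesions.

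All of this limits the strength of the point. It leaves standing that the only items named and analyzed under a cost label omit the intervention's own resource use and most SRE care.

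**Conclusion.** The concern holds as a matter of endpoint content and labeling. The only named and analyzed surrogates of health care cost are hospitalizations for SREs. They are tilted toward RT in expectation, provided that admission share and stay per SRE are similar between arms, and cannot alone support a net cost conclusion. The illustration puts 5.6 vs 2.8 counted admissions beside at least 37 uncounted up-front courses in arm 2 and at most about 22 SRE-driven courses in arm 1. It rests on one lesion and at most one SRE per patient, the planning rates, and external admission figures carried equally into both arms; it is not a forecast. The point concerns one secondary endpoint and leaves the primary endpoint and the sample size of 74 unaffected.

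**What to change.** In the abstract, Study endpoints and Planned statistical analysis, define the resource endpoint identically for both arms, from randomization to death or 12 months, and report together:

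1. all spine RT courses and fractions, protocol and palliative;
2. spine interventional procedures and operations;
3. all-cause admissions and hospital days, with SRE-related admissions as a subset.

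At minimum, relabel the endpoint 'SRE-related hospitalization' and draw no health-care-cost conclusion from it.

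The cost is small. Up-front RT, palliative RT, procedures and surgery are already recorded as the intervention or as primary-endpoint components, although fraction counts may need to be abstracted. All-cause admissions need modest extra record abstraction. The sponsor should accept that the fuller result may be less favorable to early RT. Treatment, visits and sample size do not change.
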